### Procedure for unblinding if needed {17b}

The trial design is open label; therefore, there is no unblinding procedure.

## Data collection and management

### Plans for assessment and collection of outcomes {18a}

#### Data management and data safety

All clinical data will be securely stored in the electronic case report form (eCRF) utilizing the SecuTrial® System, a web-based data management application. SecuTrial® includes automated range checks, completeness checks, consistency rules, audit trails, user-right management, electronic query handling, and validation procedures to ensure data quality before database lock. Data will be retrieved from the electronic health records of the patients and from the information entered into the application. Data entered will be stored on server systems compliant with DIN ISO 27001, located in Germany. The cloud computing regulation of the Bundesinstitut für Sicherheit in der Informationstechnologie (BSI, National Institute for Cybersecurity) C5 will be complied with. Only authorized and trained members of the study team will have access to enter data, systematically ensuring accuracy and completeness. Investigators responsible for postoperative complication assessment will receive centralized training in the application of the Clavien–Dindo classification to ensure consistent complication grading across centers. Clinical data will be pseudonymously documented using specific identification numbers. Participants will remain anonymous in all study reports, with no identifiable personal information disclosed. Study data will be integrated into statistical software and analyzed by the Institute of Biostatistics and Mathematical Modeling at Frankfurt.

### Plans to promote participant retention and complete follow-up {18b}

The patients will receive extensive information about the study setup and requirements during the recruitment. The importance of completion of the follow-up will be stressed. Patients are allowed to stop at any time during the study and are not obliged to give a reason to discontinue. Usage of the application is done remotely so at the convenience of every patient. Throughout the follow-up period, the researchers will check responses and if necessary, contact patients for completion of their follow-up.

### Data management {19}

All clinical data will be securely stored in the electronic case report form (eCRF) utilizing the SecuTrial® System. (S)AEs will be recorded in the eCRF. Backups on the protected research server will be made regularly (once per 3 months). Informed consent and end-of-trial dates will be recorded in the electronic patient dossier and signed paper forms will be stored within our hospital in a locked room.

#### Data monitoring

Regular monitoring will be conducted by the data monitoring committee following Good Clinical Practice guidelines and DIN ISO 14155 standards. Monitors will review data for protocol compliance and accuracy, ensuring alignment with source data documents such as electronic health records and The Prehab App. Monitoring activities will guarantee completeness of data entry, accuracy of study management, and documentation of safety measures.

Original data will be printed, transferred into the eCRF, and kept in the ISF as original at each site for 15 years.

### Confidentiality {27}

The study will adhere to the Declaration of Helsinki and Good Clinical Practice standards outlined in DIN ISO 14155, Medical Device Regulation, and the Medical Devices Implementation Act. All documents will be stored safely in confidential conditions following the ISO 27001 and ISO14155 requirements for safe data storage. On all study-specific documents, other than the signed consent, the participant will be referred to by the study participant number/code, not by name. The trial staff will ensure that the participants’ anonymity is maintained. The participants will be identified only by initials and a participant’s ID number on the CRF and any electronic database. All documents will be stored securely and will be only accessible by trial staff and authorized personnel. The study will comply with the Data Protection Act 1998 which requires data to be anonymized as soon as it is practical to do so; the key to the identification code list will only be available to the research team during the study and will be documented and safeguarded by the principal investigator according to research guidelines after completion of the study. No patient identification details will be reported in publications.

### Plans for collection, laboratory evaluation, and storage of biological specimens for genetic or molecular analysis in this trial/future use {33}

Blood samples will be collected upon trial inclusion and preoperatively. Laboratory evaluations will be conducted according to general evaluations in the participating hospitals after SOP. Biological sampling is done according to the standards of the UCT in the general bio database. Formalin-fixed paraffin-embedded (FFPE) tumor specimens are centrally biobanked and analyzed. They will be used in future studies.

## Statistical methods

### Statistical methods for primary and secondary outcomes {20a}

Data will be analyzed using IBM SPSS (version 29 or more current version, if applicable). Surgical procedures and indications will be categorized based on OPS and ICD-10 codes. Subgroup analyses will be conducted using chi-square testing, *T*-testing, Kaplan–Meier survival analysis, and multivariate regression analysis. The center will be included as a stratification variable. Data will be descriptively evaluated and tested for normal distribution with the Kolmogorov–Smirnov test with Lilliefors correction. Data will be expressed as median or means with standard deviation and interquartile and/or odds ratios with 95% confidence intervals where appropriate. Survival data will be calculated as time intervals from the date of their death to the date of operation, respectively be censored, if they are alive at their last visit/contact. Subgroup analyses will be conducted for predefined categories including cancer versus non-cancer surgery, abdominal versus non-abdominal procedures, and higher-risk versus lower-risk patients. Surgical category will additionally be included as a covariate in multivariable analyses to account for potential heterogeneity in baseline risk. The primary analysis will follow the intention-to-treat principle. Multivariable regression models will be used to assess treatment effects while adjusting for study center and relevant baseline characteristics. Where appropriate, mixed-effects regression models including study center as a random effect will be applied to account for the multicenter study design.

Costs will be derived from data recorded in the electronic case report form (eCRF). Costs for a day on ICU are 1500€/day, for a day on the IMC 1000€, and on general ward 500€. The DRG generated by each case will be subtracted from the sum on each treatment unit and the final sums compared between the arms. This is a two-sided approach using *T*-testing of two independent groups and a *p *value < 0.05 is regarded clinically significant.

The 95% confidence interval of the fixed effect size will be used to assess whether the treatment difference reaches the minimally clinically important difference.

All (S)AE(I)s will be summarized and recorded including the nature, date and time of onset, date of resolution, determination of seriousness, severity, action taken, outcome, and possible causality to study treatment. SAE data will be presented in a descriptive manner.

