### Outcomes {12}

#### Descriptive measures, survival analyses, and cost analyses

Primary outcome: occurrence of any postoperative complication within 90 days after surgery according to the Clavien–Dindo classification (grades I–V).

Secondary outcomes: 1-year overall survival, 6-min walking distance, QLQ-C30 quality of life score, adherence and compliance, device failures, length of stay, days on ICU/IMC, readmission rates, hospital costs.

There will be an intention to treat analysis of all included patients fulfilling the in- and exclusion criteria. Data will undergo descriptive evaluation and assessment for normal distribution utilizing the Kolmogorov–Smirnov test with Lilliefors correction. Results will be presented as median or mean with standard deviation and interquartile ranges, and/or odds ratios with 95% confidence intervals, where applicable. Survival data will be computed as the time interval from the date of surgery to the date of death, or until censoring if patients are alive at their last visit/contact.

An intention-to-treat analysis will encompass all enrolled patients meeting the predetermined inclusion and exclusion criteria. Additionally, a per-protocol analysis will be conducted.

Compliance analysis in the intervention group includes the analysis of the number of exercises performed and the exercising within the predefined thresholds. We do expect a total of 191 6-MWTs delivering 65,000 pulse points and approximately 53 Mio. pulse points from 191 patients performing 10 exercises of 47 min each during the program that will define compliance as outlined in the following. Compliance of patients in the intervention group will be categorized according to the app algorithm (green: >75% of exercises performed and >75% of all measured values are green or yellow, yellow: 50–75% of exercises performed and 50–75% of all measured values are green or yellow, red: <50% of exercises performed and <50% of all measured values are green or yellow). Comparative compliance in the control group and the intervention group will be based on a descriptive comparison of the weekly safety calls in each group during the interventional phase as PROM analysis.

Surgical procedures and indications will be categorized based on OPS and ICD-10 codes. Subgroup analyses will be conducted using chi-square testing, *T*-testing, Kaplan–Meier survival analysis, and multivariate regression analysis.

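### A normality test with no stated use other than an open choice of median or mean could leave ICU days, QLQ-C30 and cost described by medians that fit neither the data nor the cost t-test (minor)

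*Protocol article*

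**What the plan says.** The same pairing appears twice in the protocol article.

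- Section {20a}, Statistical methods, in two consecutive sentences: data are to be "tested for normal distribution with the Kolmogorov–Smirnov test with Lilliefors correction. Data will be expressed as median or means with standard deviation and interquartile" ranges. The second sentence in full reads: "Data will be expressed as median or means with standard deviation and interquartile and/or odds ratios with 95% confidence intervals where appropriate".
- Outcomes {12}, under Descriptive measures, survival analyses, and cost analyses: "assessment for normal distribution utilizing the Kolmogorov–Smirnov test with Lilliefors correction", then "Results will be presented as median or mean with standard deviation and interquartile ranges, and/or odds ratios with 95% confidence intervals, where applicable".

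Neither place gives a significance level for the test, a list of variables to be tested, or a rule linking the result to the summary.

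For costs, {20a} builds a net figure per patient: "The DRG generated by each case will be subtracted from the sum on each treatment unit and the final sums compared between the arms". It then fixes the comparison: "This is a two-sided approach using" a t-test for two independent groups. That test is not conditional on normality. Elsewhere in {20a}, t-tests are named for subgroup analyses, and treatment effects are to come from multivariable or mixed-effects regression. No between-arm test is named specifically for overall stay, ICU days or QLQ-C30.

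Outcomes {12} lists 6-minute walking distance, QLQ-C30, length of stay, ICU/IMC days and hospital costs as secondary outcomes. Section {16a} stratifies randomisation by center and by diagnostic/surgical category.

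**The concern.** A normality test placed directly before a choice of mean or median is naturally read as the way that choice is made. If it is used so, the summary depends on a test that, at this sample size, reacts to rounding and to zeros rather than to any problem with the mean. Three outcomes are exposed:

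- **Cost.** The planned t-test compares means, but the description could be a median.
- **ICU days.** When more than half the patients have no ICU stay, the median is 0 whatever happens to the others.
- **QLQ-C30.** On a coarse scale, two medians can fall on the same step while the means differ.

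If the test is not meant to decide, it has no stated purpose and the choice of summary stays open in an open-label trial. Either way the sentence needs repair.

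**Working it through.** **Sample size (Sample size {14}).** For 60% vs 45%, two-sided alpha 0.05 and 80% power:

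n = [1.960 × √(2 × 0.525 × 0.475) + 0.842 × √(0.60 × 0.40 + 0.45 × 0.55)]² / 0.15² = (1.384 + 0.588)² / 0.0225 ≈ 173 per arm.

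173 × 1.1 = 190.3, so 191. This matches the protocol, and 191 per arm is used below.

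**Assumptions.** The protocol gives no SD or distribution for any continuous outcome. Everything below rests on assumed shapes and shows what is plausible; it does not predict this trial's data.

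**Step 1. How often does the Lilliefors test reject at 5% with 191 patients?** (200 to 400 simulated samples per setting)

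| Outcome | Assumed shape | Rejected |
|---|---|---|
| Stay, whole days | lognormal, median 10, log-SD 0.2 to 0.7 | about 100% |
| ICU days | 30% or 60% zeros, remainder geometric | about 100% |
| QLQ-C30 scale | normal, mean 65, SD 15 to 28, on 8.33-point steps | about 100% |
| Cost net of DRG | the protocol's day rates, lognormal DRG, 19 settings | 68 to 99% |
| 6-minute walk | normal | about 4% |
| 6-minute walk | moderately left-skewed | 73% |

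At 173 per arm the cost range is 59 to 98%. For QLQ-C30, rounding a normal variable to a grid is by itself nearly enough to cause rejection.

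**Step 2. Does the t-test on cost need the pre-test?** With 191 per arm and equal skewed cost distributions in both arms, the two-sided t-test rejected in 4.7% of 4,000 trials. The pre-test protects nothing here.

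**Step 3. ICU days.** Tie the scenario to the trial hypothesis: complications 60% vs 45%, half of complicated patients go to ICU, and their mean ICU stay is 4 days.

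- Mean days: 0.60 × 0.5 × 4 = 1.20 vs 0.45 × 0.5 × 4 = 0.90, a difference of 0.30.
- Share with no ICU stay: 1 − 0.30 = 70% vs 1 − 0.225 = 77.5%, so both true medians are 0.
- In simulation the medians were equal in every trial. A t-test on the means had only about 22% power, so what a median hides is the estimate, not a likely significant result.

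**Step 4. QLQ-C30.** Assume a true difference of 5 points (65 vs 70).

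- On 8.33-point steps the two medians coincide in about 55 to 71% of trials for SD 15 to 25.
- On 6.67-point steps they coincide in about 37 to 44%.
- A further run gave 34 to 68% across SDs and grids, so the overall range is about 34 to 70%.
- At SD 15 a t-test on means has about 90% power, while on the 8.33-point grid the medians are equal in about 70% of trials.

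**Step 5. Stay.** With complications 60% vs 45% and longer stays in complicated patients, means differ by 1.2 days and medians by 0.9. The median does not miss this difference.

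**The case against.** The strongest reply is that the decision rule is not in the text. Testing for normality and choosing a summary are separate sentences, the second is qualified by appropriateness, and its wording would also allow both summaries to be printed. The choice per variable may sit in the statistical analysis plan, which is not shown. This stands in part: that the test steers the summary is an inference. It is still the natural one, because the article twice states the procedure and gives it no other function.

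Several stronger readings are tempting, and the documents do not support them:

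- **That the test selects the analysis.** No switch to a rank test is written. The cost t-test and the regressions do not depend on the pre-test, and the primary endpoint is binary.
- **That the cost result could not support a statement about total cost.** Costs are tested on arithmetic means, which do scale to a total. Only the accompanying description could be a median.
- **That rejection is certain for cost.** Net cost after subtracting the DRG is less skewed than gross cost, so rejection is likely, not certain.
- **That medians miss differences in every outcome.** This is shown for ICU days and is plausible for QLQ-C30. Stay does not show it, and the documents give no IMC rate from which to judge IMC days.
- **That every outcome has a mismatch with a t-test.** For an overall comparison, only costs have a t-test written down.

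It is also fair to say that bootstrap intervals are not needed, given Step 2.

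**Conclusion.** The point holds as a minor defect in how secondary outcomes are to be reported. At 191 per arm the normality test is uninformative for ICU days and QLQ-C30, where rejection is close to certain, and mostly so for net cost, where it is likely. If it guides the summary, as the text suggests but does not say, three results follow: a possible median beside a p-value for mean cost, an ICU median of 0 in both arms despite different means, and QLQ-C30 medians that coincide in roughly a third to 70% of trials with a real 5-point difference. The sizes depend on assumed distributions, SDs and scale steps. No sample-size figure, primary result or planned test changes.

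**What to change.** In Outcomes {12} and section {20a}:

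1. Delete the Kolmogorov–Smirnov–Lilliefors test as a selector, and state that mean (SD) and median (IQR) are given for all continuous outcomes.
2. For costs, length of stay and ICU/IMC days, report the arithmetic mean difference with a 95% confidence interval, adjusted for center and diagnostic/surgical category. For costs this replaces the plain independent-groups t-test, which ignores the strata used in randomisation. A bootstrap interval is optional.
3. For QLQ-C30, report the mean difference from a model with the strata, and with the baseline score where it is collected in both arms.

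This needs no new data and no change in sample size. The cost is a revision of wording and analysis, and a few more lines of output.

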## Methods: participants, interventions, and outcomes

### Study setting {9}

Patient recruitment is taking place at 6 trial centers in Germany; the hospitals vary between university hospitals and maximum care hospitals. All participating centers are highly experienced in major surgeries. The list of study sites can be obtained upon request from the corresponding author or under https://drks.de/search/de/trial/DRKS00033612. Reporting was done according to the SPIRIT guidelines (supplements 2) [16].

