Costs will be derived from data recorded in the electronic case report form (eCRF). Costs for a day on ICU are 1500€/day, for a day on the IMC 1000€, and on general ward 500€. The DRG generated by each case will be subtracted from the sum on each treatment unit and the final sums compared between the arms. The cost analysis will be conducted from the hospital/provider perspective based on in-hospital resource utilization including ICU, IMC, and general ward stay.

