## Assignment of interventions: allocation

### Sequence generation {16a}

The patients will be randomized after eligibility confirmation, which will in most cases also be the baseline assessment day. The randomization sequence is computer-generated by an independent statistician using randomly varying block sizes and stratified by study center and diagnostic/surgical category. The allocation list is generated before study initiation and securely stored. For equal distribution of indications, sex, age, and center effects, we will create specific randomization blocks for the trial. The centers will receive envelopes with randomization information. The patients will be randomized during baseline assessment using block randomization stratified by study center and diagnostic/surgical category. This approach ensures balanced allocation of patients between treatment arms within each participating center and accounts for potential center-specific differences in surgical practice and perioperative care.

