### Limitations

There are some limitations to be considered. First, prehabilitation as understood in this study with the focus on bodily training excludes patients before cardiac surgery as well as trauma surgery patients. We do include all other surgical patients in this study, though. Furthermore, complication rates may vary across centers and surgical categories due to differences in surgical case mix and perioperative care pathways. Although the sample size calculation was based on previously published complication rates, potential center-related heterogeneity may influence the observed effect size. This will be addressed analytically by adjusting for center effects in the statistical models. Second, the follow-up period after surgery is relatively short (1 year) and long-term efficacy remains to be investigated. There might occur performance bias through different perioperative care and detection bias for subjective outcomes, but this should be negligible via training of study members and standard operating procedures. Lastly, only patients in possession of a smartphone can participate in this trial. These days, non-possession should be a rare occurrence.

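### The hospital cost conclusion rests on an unadjusted t-test although allocation is stratified by centre and surgical category, and the article does not say whether its adjusted models govern costs

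*Protocol article*

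**What the plan says.** **Cost outcome.** Section {20a} of the protocol article prices bed-days at flat rates: "Costs for a day on ICU are 1500€/day, for a day on the IMC 1000€, and on general ward 500" euros. The per-patient result is then set against reimbursement: "The DRG generated by each case will be subtracted from the sum on each treatment unit and the final sums compared between the arms" (the same sentence stands in the Outcomes section {12}). Hospital costs are a secondary outcome, listed with "length of stay, days on ICU/IMC, readmission rates, hospital costs".

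**Cost test.** The cost paragraph of {20a} names one method: "This is a two-sided approach using *T*-testing of two independent groups". It attaches a p < 0.05 rule and mentions no covariate or stratum.

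**Allocation.** Sequence generation {16a} specifies "block randomization stratified by study center and diagnostic/surgical category". The Study setting section {9} gives the number of centres: "Patient recruitment is taking place at 6 trial centers in Germany".

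**Adjusted models.** The paragraph of {20a} just before the cost text brings centre in as a stratification variable. It plans multivariable models for treatment effects adjusted for centre and baseline characteristics, adds surgical category as a covariate, and allows mixed models with a random centre effect where appropriate. None of these sentences names an endpoint.

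**The concern.** Blocking within strata keeps the arms balanced on centre and surgical category, so differences between strata largely drop out of the arm difference. A two-sample t-test does not take this into account. It estimates its standard error from the total variance, including the part between strata that the design has already removed. If the strata predict the outcome, the standard error is too large and the p-value too high on average.

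There is reason to expect some prediction. The inclusion criteria run from abdominal wall hernia repair and endocrine surgery to pancreatic, hepatobiliary and lung resection, and the only cost inputs are ward, IMC and ICU days. The Limitations section says that "complication rates may vary across centers and surgical categories due to differences in surgical case mix and perioperative care pathways". That sentence concerns complications, not costs, but complications plausibly drive bed-days.

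The abstract names lower costs beside lower morbidity as what the trial sets out to show. A needlessly conservative test under a p < 0.05 rule makes it more likely that a real cost difference is reported as none. The article also leaves two candidate cost analyses, with different p-values, and does not rank them.

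**Working it through.** **Figures in the plan.** The article gives no variance, effect size or power for costs. Its only sample size is for the primary endpoint. With 60% versus 45%, two-sided 0.05, 80% power and pooled variance:

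n = [1.96·√(2·0.525·0.475) + 0.8416·√(0.60·0.40 + 0.45·0.55)]² / 0.15² = (1.3842 + 0.5876)² / 0.0225 = 172.8, so 173 per arm, as stated.

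This reproduces the plan's figure but does not power the cost comparison.

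**Set-up for costs.** Let R² be the share of the variance of cost minus DRG that centre and surgical category explain. The documents do not give it, so it is varied. Let k = √(1 − R²). With 1:1 allocation balanced within strata, the true standard error of the arm difference is k times the one the t-test uses. Fix the effect at the size for which a t-test would have 80% power if R² were 0, that is 1.96 + 0.8416 = 2.80 standard errors. The sample size then cancels, so 173 and 191 per arm give the same results.

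- Excess of the t-test standard error: 1/k − 1
- True type I error of the t-test: 2·Φ(−1.96/k)
- Power of the t-test under stratified allocation: Φ((2.80 − 1.96)/k)
- Power of the stratum-adjusted analysis: Φ(2.80/k − 1.96)

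Example, R² = 0.20: k = 0.894. The excess is 1/0.894 − 1 = 11.8%. Type I error is 2·Φ(−2.19) = 2.8%. Power is Φ(0.94) = 82.7% unadjusted and Φ(1.17) = 87.9% adjusted.

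| Assumed R² | SE too large by | True type I error | Power, t-test | Power, adjusted | Forgone (points) |
|---|---|---|---|---|---|
| 0 | 0% | 5.0% | 80.0% | 80.0% | 0 |
| 0.05 | 2.6% | 4.4% | 80.6% | 82.0% | 1.4 |
| 0.10 | 5.4% | 3.9% | 81.3% | 84.0% | 2.7 |
| 0.20 | 11.8% | 2.8% | 82.7% | 87.9% | 5.2 |
| 0.30 | 19.5% | 1.9% | 84.3% | 91.8% | 7.5 |

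**Check by simulation.** The closed form assumes perfect balance within strata and no cost in degrees of freedom. A simulation relaxed both: 346 patients (2 × 173), 6 centres, 6 assumed categories, permuted blocks, log-normal errors and 1,500 replicates.

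| Assumed R² | SE ratio | Null rejection, t-test / adjusted | Power, t-test / adjusted |
|---|---|---|---|
| 0 | 1.00 | 5.5% / 5.7% | 79.3% / 79.3% |
| 0.10 | 1.05 | 3.6% / 4.8% | 81.1% / 83.9% |
| 0.20 | 1.12 | 2.9% / 4.5% | 82.4% / 86.9% |
| 0.30 | 1.20 | 2.4% / 5.7% | 83.9% / 90.9% |

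Monte Carlo error near 5% is √(0.05·0.95/1500) ≈ 0.6 points. A second simulation (382 patients, 4 assumed categories, 3,000 runs, log-normal errors) gave power of 82.4% versus 84.7% at R² = 0.10 and 85.9% versus 91.9% at R² = 0.30, so 2.3 and 6.0 points forgone. The direction agrees throughout, and at R² of 0.20 and above the simulated gains are below the closed form.

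**The case against.** **Adjustment is already planned.** The heading of {20a} covers primary and secondary outcomes, and its model sentences are not limited to the primary endpoint. A reader might infer that costs get no adjusted analysis at all, and the article does not support that. What remains is narrower: the cost paragraph comes later, names its own unadjusted test and ties the conclusion to that test's p-value, and nothing says that the models take precedence.

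**The loss is assumed.** This stands. No R² is given, and at R² = 0 nothing is lost. The DRG varies by case, so subtracting it may remove part of the case-mix difference. It may also leave or add some, because the cost side holds only bed-days at flat rates. The article does not settle this.

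**No inference goes wrong.** Also right. The type I error stays at or below 5%. Costs are secondary with no power target, and for the effect considered the t-test keeps at least its nominal 80% power. A possible gain is forgone; no planned power is lost.

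**No cost interval is planned.** One might say that the trial's cost confidence interval is too wide. The cost paragraph plans none, and the 95% interval at the end of {20a} belongs to a fixed effect size, which is model language. The point concerns the standard error behind the p-value.

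**This is for the SAP.** Covariate lists for secondary endpoints are often left there, and a SAP exists by reference. But the article does not leave the method open: it names a test. If the SAP already makes the adjusted model the main cost analysis, the two texts only need aligning.

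**Conclusion.** The point holds as an almost free gain in efficiency and clarity. The article ties the cost conclusion to a test that ignores both randomisation factors, and does not say whether its adjusted models govern costs. To the extent that the strata predict cost minus DRG, the test is conservative. Over assumed R² of 0 to 0.30, the standard error is 0 to about 20% too large, the true type I error falls from 5% to about 2%, and 0 to about 7.5 power points are forgone by the closed form (6 to 7 at the upper end in simulation). At R² of 0.10 or less the gain is under 3 points.

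The size rests wholly on the assumed R², on near-balance within strata, and on an effect set at 80% nominal power. Two stronger readings fail. The t-test is not invalid, because its error is on the safe side. The criticism does not extend to length of stay or ICU/IMC days, because the article fixes no unadjusted test for those outcomes. The primary endpoint is untouched.

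**What to change.** In the cost paragraph of {20a}, state that the main cost comparison is a linear model of the per-patient sum (unit-day costs minus DRG) on treatment arm, with study centre and diagnostic/surgical category as covariates and sparse categories pooled by a rule set in advance. Report the adjusted mean difference in euros with a 95% CI from robust or bootstrap standard errors, since costs are likely to be skewed. Keep the unadjusted t-test as a sensitivity analysis.

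The cost is small. No new data are needed: centre is known, and {20a} already plans to classify procedures and indications by OPS and ICD-10 codes. Six centres use 5 degrees of freedom, and 4 to 10 pooled categories use 3 to 9, so 8 to 14 in all with 382 patients. The pooling rule must be written down before the data are analysed.
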